### Randomisation and allocation concealment

Eligible participants will be randomised following baseline data collection of primary and secondary outcome measures to receive either unloading shoes or control shoes. Randomisation will be by random permuted blocks of size from 6 to 12 and stratified by radiographic disease severity (Kellgren and Lawrence grades 2, 3 and 4 [29]). The randomisation schedule will be prepared by the study biostatistician. To conceal randomisation, consecutively numbered, sealed, opaque envelopes will be used and kept in a locked location.

Participants will be blinded to which treatment group they are allocated and allocated shoes will have no identifying model or brand. The unloading shoes are visually similar to the control shoes to maintain participant blinding. Participants will be asked to indicate which group they believe they are in order to measure the success of blinding. As all primary and secondary outcomes are participant-reported questionnaires, and participants will be blinded to group allocation, the assessor is also blinded in this study. An investigator, who will also be blinded to group allocation, will oversee administration of all primary and secondary outcome measures. Additional biomechanical and gait analysis measures (that will not be used to determine treatment efficacy but will be used in subsequent analyses to evaluate predictors of treatment response) will be conducted by another investigator who is not blinded to group allocation by necessity due to the nature of the biomechanical testing procedures.

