### Sample size calculations

The trial is powered to detect clinically important changes in the primary outcomes of knee pain on walking (NRS) and change in physical function (WOMAC). The minimum clinically important difference to be detected in OA trials is a change in pain of 1.8 units (out of 10) [41] and change in function of six units (out of 68) [42]. Our calculations are based on SD’s from our unpublished pilot data of the effects of unloading shoes, and on control group data from our previous RCT of lateral wedged insoles [43]. We assume a between-subject SD of 2.5 for pain and 10.5 units for WOMAC physical function, and a baseline to 12-month correlation in scores of 0.29 for pain and 0.51 for physical function. These assumptions, together with an analysis of covariance adjusted for baseline scores, require a sample size of 41 participants per group to achieve 90% power to detect the minimum clinically important difference in pain. A similar analysis for function scores requires 65 participants per group. Allowing for a 20% attrition rate, we will recruit 82 participants per arm, or 164 participants in total.

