### Statistical analyses

Our biostatistician will analyse data in a blinded manner, with p values less than 0.05 considered significant. Main comparative analyses between groups will be performed using intention-to-treat. This analysis will include all participants including those who have missing data and those who do not fully adhere to the protocol. To account for missing data, multiple imputation of missing follow-up measures, assuming data are missing at random and follow a multivariate normal distribution, will be performed as a sensitivity analysis.

Demographic characteristics, as well as baseline scores on primary and secondary outcome measures, will be presented to assess baseline comparability of treatment groups. These variables will also be examined for those participants who withdraw from the study and those who remain.

Descriptive statistics will be presented for each group as the mean change (standard deviation, 95% confidence intervals) in the outcomes from baseline to each time-point. For continuous outcome measures, differences in mean change (baseline minus follow-up score) will be compared between groups using linear regression random effects modelling adjusted for baseline values of the outcome. Model diagnostic checks will utilise residual plots. Similar regression models for binary and ordinal outcome measures will use random effects logistic and proportional odds models, respectively. We will also perform a per protocol analysis as appropriate.

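### Randomisation is stratified by Kellgren-Lawrence grade, but the stated model for continuous outcomes does not name it; standard errors are slightly conservative if the grade is prognostic (minor).

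*Protocol article*

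**What the plan says.** Under Randomisation and allocation concealment, the protocol article states: "Randomisation will be by random permuted blocks of size from 6 to 12 and stratified by radiographic disease severity". The strata are KL grades 2, 3 and 4.

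Under Statistical analyses, mean changes in continuous outcomes are to be "compared between groups using linear regression random effects modelling adjusted for baseline values of the outcome". The baseline value is the only covariate mentioned. Binary and ordinal outcomes get analogous random-effects logistic and proportional-odds models. The significance rule is "with p values less than 0.05 considered significant".

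The Sample size calculations section describes the same adjustment: an analysis of covariance on the baseline score, again without KL grade. The stated results are 41 per group for pain and, for function, "A similar analysis for function scores requires 65 participants per group".

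**The concern.** Blocking within KL strata keeps the arms close to balanced on grade, so differences between grades contribute almost nothing to the sampling error of the treatment difference. A model that omits grade cannot know this. It counts between-grade variation as residual noise and reports a standard error for a less well balanced design than the one used.

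If the grade carries information about the 6-month outcome beyond the baseline score, confidence intervals are then wider than they need be, the test rejects less often than 5% under the null, and a little power is forgone. Otherwise nothing is lost. What is at stake is precision and agreement between design and analysis, not bias.

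**Working it through.** **Inputs from the article (Sample size calculations).** Target differences 1.8 (pain) and 6 (function); "between-subject SD of 2.5 for pain and 10.5 units for WOMAC physical function"; baseline to follow-up correlations 0.29 and 0.51; 90% power; 20% attrition; 82 per arm. The article quotes the correlations to 12 months; they are used here as given for the 6-month endpoint. A two-sided 5% test is assumed.

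**Assumption.** R² is the share of residual variance, after baseline adjustment, that KL grade explains. The article gives no value, so 0 to 10% is shown.

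**The plan's own figures.** n per group = 2 × (1.960 + 1.282)² × (SD/difference)².
- Pain: 2 × 10.51 × (2.5/1.8)² = 40.5, so 41.
- Function: 2 × 10.51 × (10.5/6)² = 64.4, so 65.
- Attrition: 65/0.8 = 81.25, so 82 per arm and 164 in total.

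These match the article, but they use the full SD. With the baseline-adjusted SD, SD × √(1 − r²), the same formula gives 38 and 48. That is a separate matter; here it means that power has to be shown on both bases.

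**Standard error and type I error.** With KL grade balanced by design but omitted from the model, model SE/true SE = 1/√(1 − R²), and true type I error = 2 × [1 − Φ(1.96/√(1 − R²))].

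| R² | SE overstated by | True type I error |
|---|---|---|
| 0 | 0 | 5.0% |
| 2% | 1.0% | 4.8% |
| 5% | 2.6% | 4.4% |
| 10% | 5.4% | 3.9% |

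**Power for function, 65 completers per arm.** Let m = SD × √(2/65) and t = m × √(1 − R²). Power without KL grade = Φ((6 − 1.96m)/t); power with it = Φ(6/t − 1.96).

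- Baseline-adjusted SD: 10.5 × √(1 − 0.51²) = 9.03, so m = 1.584. At R² = 10%, t = 1.503: without, Φ(1.926) = 97.3%; with, Φ(2.032) = 97.9%.
- Full SD: m = 10.5 × √(2/65) = 1.842. At R² = 10%, t = 1.747: without, Φ(1.368) = 91.4%; with, Φ(1.474) = 93.0%.

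| R² | Adjusted SD: without / with | Full SD: without / with |
|---|---|---|
| 0 | 96.6% / 96.6% | 90.3% / 90.3% |
| 5% | 97.0% / 97.3% | 90.9% / 91.7% |
| 10% | 97.3% / 97.9% | 91.4% / 93.0% |

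For pain with the adjusted SD, power at 65 per arm is 99.0% either way at R² = 0, and 99.3% against 99.5% at 10%.

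**Simulation check.** Function, stratified permuted blocks, 130 completers, 6,000 runs per setting, stratum shares assumed. At R² = 10%, the model without KL grade had a mean model SE of 1.59 against an empirical SE of 1.49 to 1.51, type I error 3.7% and power 96.7%. With KL grade, type I error was 4.6% and power 97.5%. At R² = 0 the two models did not differ materially.

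**On the outcome scale.** At R² = 10% with the adjusted SD, the 95% interval half-width is too wide by 1.96 × (1.584 − 1.503) = 0.16 points on the 68-point function scale, against a 6-point target.

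**The case against.** **The effect is conditional, and the condition is not shown.** This stands. A reader might infer that the standard errors are too wide and that power is being thrown away. The article reports no association between KL grade and later pain or function, so neither can be stated as fact. The choice of KL grade as the only stratifier makes some prognostic value plausible, but it does not measure it.

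**Planned power is not lost.** This also stands. The sample size counts on no gain from KL grade, and power without it is at or above 90% in every scenario shown. A larger power penalty can be obtained by going beyond 10%, or by pairing the unadjusted effect of 6/10.5 = 0.57 SD with a share of variance defined after baseline adjustment. On a consistent baseline-adjusted basis the effect is 6/9.03 = 0.66 SD and the gain is about 1 point or less.

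**The article may condense a fuller plan that names KL grade.** This is possible, and the text does not say that baseline is the sole covariate. But the adjustment is described in two sections, each time without the stratifier, and nothing points to a longer list. The random effect is not named; with primary outcomes measured at 3 and 6 months, participant is a more natural reading than KL stratum. The mismatch in the stated model therefore remains.

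**The argument does not carry over to the logistic and proportional-odds models.** Correct. There, adding a covariate changes the target to an odds ratio conditional on that covariate, and the standard error figures do not apply.

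**Conclusion.** The concern holds in limited form. The stated model for continuous outcomes omits the factor by which the trial randomises. If KL grade explains 0 to 10% of the variance left after baseline adjustment (an assumption), the standard error is overstated by 0 to about 5.4% and type I error lies between 5% and about 3.9%. The power forgone for function is 0 to about 1 point on the baseline-adjusted SD, or up to about 1.6 points on the full SD.

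Any error is in the conservative direction, and the treatment estimate for continuous outcomes is unbiased. The mismatch and the direction of its effect are firm; its size is not known from the article. This is a minor improvement, not a threat to the trial's validity.

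**What to change.** In Statistical analyses, extend the adjustment for continuous outcomes to the baseline value of the outcome and KL grade, entered as a three-level categorical fixed effect (2, 3, 4). If a fuller analysis plan already does so, bring the article's description into line with it.

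KL grade may also be added to the logistic and proportional-odds models, with a note that the odds ratio is then conditional on grade. The global ratings of change are collected only at follow-up and have no baseline value to adjust for, so KL grade is a natural design covariate there.

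The cost is one phrase and two degrees of freedom. The grade is known for every participant before randomisation, so no new data are needed. If it proves not to be prognostic, almost nothing is lost; naming it now also avoids choosing covariates after the data are seen.

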### Timelines

The application for project funding was successful in October 2012 and funding commenced in June 2013. Ethics approval was obtained from the Human Research Ethics Committee of the University of Melbourne in February 2013. Recruitment commenced in August 2013 will be completed in December 2015. The trial is due for completion in June 2016 when all participants will have completed 6-month follow-up.

## Discussion

This paper has presented the theoretical rationale, as well as the protocol, for a RCT that is testing the efficacy of specially-designed unloading shoes for managing the symptoms of knee OA. The findings of this study will help determine whether unloading shoes can relieve pain and/or improve self-reported physical function over 6 months of use. Given that clinical guidelines emphasise appropriate footwear should be worn by people with knee OA [17], and there is scant evidence from clinical trials to inform optimal footwear choices in this population, findings from the current RCT will assist clinicians and people with knee OA in selection of appropriate footwear to manage symptoms of OA.

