Clinical guidelines emphasise that appropriate footwear should be worn by people with knee OA [17]. This recommendation is based on expert opinion given the scant research evidence available. Wearing shoes significantly *increases* medial knee load compared to barefoot walking [18,19]. Recent research, by ourselves and others, has developed specialised shoes for people with knee OA with variable-stiffness soles that are denser laterally compared to medially in order to reduce the KAM [20-22]. Thus, when weightbearing, the greater medial compressibility effectively creates a laterally angled shoe that reduces the frontal plane lever arm of the ground reaction force at the knee joint centre, reducing the KAM [23,24]. These types of modified shoes can immediately reduce the KAM by 3.5-7.9% in people with medial knee OA [20,25]. In a single case study involving a patient with an instrumented knee replacement, variable-stiffness shoes reduced the peak KAM by 13.3% and medial joint contact force by 12.3% [22]. Furthermore, change in KAM correlated with change in contact force, validating the load-modifying effects of unloading shoes for knee OA.

Relative to their biomechanical effects, there is very little known about whether unloading shoes can reduce the pain and physical dysfunction associated with knee OA. There is only one randomized controlled trial (RCT) evaluating clinical benefits of variable-stiffness unloading shoes for knee OA [25,26]. The unloading shoes resulted in significant within-group pain reductions after 6 and 12 months of use, however the change in symptoms was not significantly different to that seen in the group wearing control shoes. This may be because of the relatively small sample size utilized (n = 79) and/or the large drop-out rate in the control group (n = 13 out of 39, 33%) by 6 months. Further RCTs are required before the efficacy of unloading shoes for managing the symptoms of OA can be known.

The primary aim of this study is to evaluate the efficacy of specialized unloading shoes on OA-associated symptoms in people with knee OA. We hypothesise that unloading shoes will reduce pain and improve self-reported physical function after 6 months when compared to control shoes.

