### Outcome measures

Table 1 summarises the outcome measures that are being collected to determine treatment efficacy. Our primary outcomes are recommended validated measures of pain and physical function for knee OA [31]. These will be measured at baseline, 3 months and 6 months. Conclusions regarding treatment efficacy will be based on the changes in primary outcome measures from baseline to 6 months. Our two primary outcomes are:

**Table 1 T1:** Summary of primary and secondary outcome measures collected to determine treatment effectiveness

**Outcome**	**Measurement tool**

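### The protocol names two primary outcomes, each judged at p < 0.05, without settling whether efficacy needs one or both; if either suffices, the two-sided familywise error is about 7–10%

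*Protocol article*

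**What the plan says.** All references are to the Protocol article.

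- **Outcome measures** introduces the pair with "Our two primary outcomes are" and lists walking pain (NRS) and WOMAC physical function. It adds: "Conclusions regarding treatment efficacy will be based on the changes in primary outcome measures from baseline to 6 months". The plural is used, and nothing says how the two results combine.
- **Statistical analyses** sets a single threshold: "Our biostatistician will analyse data in a blinded manner, with p values less than 0.05 considered significant". It gives no joint rule, order of testing or division of alpha.
- **Background** states: "We hypothesise that unloading shoes will reduce pain and improve self-reported physical function after 6 months when compared to control shoes".
- **Discussion** says the findings will help determine "whether unloading shoes can relieve pain and/or improve self-reported physical function over 6 months of use".
- **Sample size calculations** sizes each outcome on its own, for a "change in pain of 1.8 units (out of 10") and a "change in function of six units (out of 68"), giving 41 and 65 per group.

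**The concern.** The article fixes the number of primary outcomes, the threshold and the basis for concluding efficacy, but not the rule that links them. The two sentences that come closest to a rule point different ways: the hypothesis predicts both benefits, while the Discussion contemplates one or both.

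This matters when the results split. If pain reaches p < 0.05 and function does not, a reader of the Background may say the hypothesis was not met, and a reader of the Discussion may say the shoes work. The abstract promises an answer on whether the shoes are efficacious, and the Discussion says the findings will help clinicians and patients select footwear. A rule chosen after the results are known would not be credible. If the looser rule is the one applied, the stated 0.05 does not hold for the overall conclusion.

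**Working it through.** **Step 1: what alpha each outcome was given.** Inputs from Sample size calculations: differences 1.8 and 6; SDs 2.5 and 10.5; power 90%. The document does not state sidedness, so two-sided 0.05 is tried. Per group, n = 2(1.960 + 1.282)² SD²/Δ².

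- Pain: 2 × 10.51 × 2.5²/1.8² = 40.5, so 41.
- Function: 2 × 10.51 × 10.5²/6² = 64.4, so 65.
- Attrition: 65/0.80 = 81.25, so 82 per arm and 164 in total.

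All stated figures are reproduced, so each outcome was sized at the full two-sided 0.05. (The match is to the SDs without baseline adjustment. Using SD√(1 − r²), with the stated correlations of 0.29 and 0.51, gives 38 and 48. That is a separate matter, but it is why power is shown on both bases in step 4.)

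**Step 2: error if either outcome suffices.** With no effect on either outcome, let Z₁ and Z₂ be standard normal test statistics with correlation ρ. The document gives no ρ, so a range is assumed.

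- Two-sided familywise error = 1 − P(|Z₁| < 1.96, |Z₂| < 1.96). At ρ = 0 this is 1 − 0.95² = 9.75%.
- False claim of benefit = 1 − P(Z₁ < 1.96, Z₂ < 1.96), with Z positive when the unloading shoes do better. At ρ = 0 this is 1 − 0.975² = 4.9%.

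| ρ (assumed) | Either significant, any direction | Either significant, in favour of unloading shoes |
|---|---|---|
| 0 | 9.75% | 4.9% |
| 0.3 | 9.5% | 4.8% |
| 0.5 | 9.1% | 4.5% |
| 0.7 | 8.3% | 4.2% |
| 0.8 | 7.8% | 3.9% |
| 0.9 | 7.0% | 3.5% |

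The single-outcome references are 5% and 2.5%. On either basis the inflation is about 1.4-fold at ρ = 0.9 (7.0/5), rising to about 2-fold at ρ = 0.

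**Step 3: error if both are required.** A false claim then needs the outcome with no true effect to reach p < 0.05, so the error is at most 5% two-sided. There is no inflation and no adjustment is needed.

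**Step 4: power with 65 completers per arm.** The noncentrality is Δ/(SD√(2/65)).

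- ANCOVA basis: residual SDs 2.5√(1 − 0.29²) = 2.39 and 10.5√(1 − 0.51²) = 9.03, giving 4.29 (pain) and 3.79 (function).
- Unadjusted SDs: 4.10 and 3.26.

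Holm compares the smaller p-value with 0.025 and, if that passes, the larger with 0.05. Simulated power for ρ from 0.3 to 0.7:

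| Basis | Holm: function | Holm: pain | Holm: both | Both required at 0.05 |
|---|---|---|---|---|
| ANCOVA as stated | about 96% | 98.5–99% | about 96% | about 96% |
| Unadjusted SDs | about 90% | 97–98% | 89–90% | 89–90% |

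For comparison, unadjusted testing at 0.05 gives function power of 96.6% and 90.3% on the two bases. Plain Bonferroni at 0.025 gives about 94% and 84–85%.

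**Step 5: how often results would split.** Even if both assumed effects are real, exactly one outcome reaches 0.05 in about 3–4% of trials (ANCOVA) or 9–10% (unadjusted SDs), and more often if one effect is smaller than assumed.

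**The case against.** A reader might infer that the protocol lets a benefit on either outcome count as efficacy, and that the chance of a false efficacy claim is therefore 8–10%. The documents do not support that as stated, for three reasons.

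- No Methods section says that either outcome suffices. The only support is one closing sentence of the Discussion, which describes what the trial may show and is not worded as a decision rule.
- The 8–10% counts false significance in both directions, including results against the unloading shoes. A false claim of benefit is about half that. The two-sided figure also falls below 8% once the correlation reaches 0.8.
- If both outcomes are required, nothing is inflated.

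It can also be said that the Background and the Discussion are compatible: a trial may predict both benefits and report each separately. A split result would then read as benefit on one outcome and none shown on the other. That is a reasonable reading, but it is the one under which each outcome can support its own claim at 0.05, so the error in step 2 applies to it.

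Finally, the choice of multiplicity procedure is commonly left to a statistical analysis plan, and this is a condensed article. Its absence alone would not be a finding. What stands is that the article itself states the threshold, the two outcomes and the basis for the efficacy conclusion, and words the link between the outcomes in two different ways.

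**Conclusion.** The point holds as an unsettled and inconsistently worded success rule, with a conditional error rate attached. If either outcome suffices, as the Discussion suggests, the two-sided familywise error is about 7–10% and the chance of a false claim of benefit about 3.5–4.9% against 2.5%. If both are required, as the hypothesis suggests, there is no inflation.

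The ranges rest on jointly normal test statistics, no effect on either outcome, two-sided tests (inferred from the stated sample sizes) and a correlation assumed between 0 and 0.9. The power figures rest on the protocol's own differences and SDs, and the ANCOVA figures also on its correlations, which it labels as baseline to 12 months although the endpoint is at 6 months.

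The point does not extend to the secondary outcomes or the 3-month results. Trial design, Procedure and Outcome measures already make 6 months the primary time-point and rest efficacy on the primary outcomes.

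**What to change.** Before unblinding, add one sentence to Statistical analyses that adopts one of these rules:

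1. The two 6-month primary comparisons are tested by Holm (or Hochberg) at a familywise two-sided 0.05, and benefit is claimed only for the outcome or outcomes that pass. This fits the wording of the Discussion.
2. Efficacy is concluded only if both comparisons reach two-sided p < 0.05. This fits the wording of the hypothesis.

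Then bring the Background hypothesis, the sentence on efficacy conclusions in Outcome measures, and the Discussion into line with the rule chosen.

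The cost is a small loss of power and no added participants. With 65 completers per arm, Holm lowers function power by less than one percentage point from unadjusted testing on either basis. Under the second rule, the joint power in step 4 becomes the trial's power: on the unadjusted SDs it is at or just below the planned 90%. Holm or Hochberg is preferable to plain Bonferroni, which would take function power below 90% on the unadjusted SDs. No relabelling of secondary or 3-month results is needed.
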